# Real-World Efficacy and Safety of Zishenyizhi Pill for Cognitive Impairment Associated With Cerebral Small Vessel Disease: Protocol for a Multicenter Prospective Observational Study

**DOI:** 10.2196/77661

**Published:** 2025-12-08

**Keywords:** cerebral small vessel disease, cognitive impairment, zishenyizhi pill, real-world studies, traditional Chinese medicine

## Abstract

**Background:**

Cerebral small vessel disease (CSVD) is a leading cause of vascular cognitive impairment, contributing to 36% to 67% of vascular dementia cases. Current therapies, primarily cholinesterase inhibitors, offer limited efficacy and significant adverse effects. Traditional Chinese medicine, particularly the zishenyizhi pill, which is a multiherb formulation targeting yin deficiency and blood stasis, has shown promise in preliminary studies but lacks robust clinical validation.

**Objective:**

We designed this study to evaluate the real-world efficacy and safety of zishenyizhi pill combined with conventional Western therapy for CSVD-related cognitive impairment.

**Methods:**

This multicenter, prospective, nonrandomized controlled trial enrolled 246 patients from 4 institutions in Hunan province, China. Participants were stratified into 2 groups: the intervention group received zishenyizhi pill plus standard Western therapy, whereas the control group received conventional integrated Chinese-Western therapy. Cognitive outcomes (Montreal Cognitive Assessment, Mini-Mental State Examination, Vascular Dementia Assessment Scale cognitive subscale, and Trail Making Test parts A and B), traditional Chinese medicine syndrome scores, and safety parameters were assessed over 12 weeks.

**Results:**

Participant recruitment is scheduled to commence in April 2025, with an anticipated enrollment of 246 participants by December 2026. At present, patient recruitment is underway, and preliminary analysis of medical record data is being conducted. Final data collection is expected to conclude by April 2027, with results projected for publication in September 2027.

**Conclusions:**

The anticipated findings suggest that zishenyizhi pill may improve multiple cognitive domains in patients with cognitive impairment associated with CSVD while demonstrating a favorable safety profile. If validated, zishenyizhi pill could serve as a safe and effective adjunctive therapy for CSVD-related cognitive dysfunction.

**Trial Registration:**

International Traditional Medicine Clinical Trial Registry ITMCTR2025000553; https://itmctr.ccebtcm.org.cn/mgt/project/view/-4790836881284495026

**International Registered Report Identifier (IRRID):**

DERR1-10.2196/77661

## Introduction

Cerebral small vessel disease (CSVD) is a clinical, imaging, and pathological syndrome caused by diverse etiologies affecting cerebral small arteries, arterioles, capillaries, venules, and small veins. Its primary neuroimaging manifestations include recent small subcortical infarcts, perivascular spaces, presumed vascular origin lacunes, white matter hyperintensities, cerebral microbleeds, and cerebral atrophy [1,2]. While patients with CSVD may present with acute-onset symptoms such as lacunar infarcts or hemorrhagic stroke, most exhibit insidious progression characterized by gradual cognitive decline, gait disturbances, affective disorders, and bladder or bowel dysfunction [3,4]. During the acute phase of CSVD evolution, pathological changes predominantly manifest as lacunar infarcts and intraparenchymal hemorrhage, accounting for approximately one-fifth of symptomatic stroke cases [5,6]. In chronic stages, the disease progresses to hemodynamically significant cerebral hypoperfusion, where persistent blood flow dysregulation induces multidimensional neural damage [7,8]. This pathophysiological cascade clinically correlates with progressive cognitive deterioration (encompassing memory, executive function, attention, language, and visuospatial domains), motor coordination deficits, autonomic dysfunction, and neuropsychiatric syndromes. Notably, CSVD represents one of the most prevalent etiologies of cognitive impairment, typically exhibiting a characteristic decline pattern marked by predominant deficits in attention, processing speed, and executive function, with relatively preserved episodic memory [9]. Epidemiological studies indicate that CSVD-related cognitive dysfunction contributes to 36% to 67% of vascular dementia (VaD) cases [10], often leading to severe functional disability, increased mortality, and substantial socioeconomic burdens.

The underlying mechanisms of cognitive impairment in CSVD remain incompletely elucidated. Neuroimaging modalities, particularly magnetic resonance imaging, have provided critical insights into potential pathophysiological correlates. Current evidence demonstrates associations among lacunar infarcts, white matter hyperintensities, cerebral atrophy, and cognitive deficits [11-13], whereas the presence and burden of cerebral microbleeds exhibit modest yet significant impacts on executive function and information processing speed [14,15]. However, the role of perivascular spaces in cognitive decline remains inconclusive based on extant data [16].

Despite the high prevalence and substantial societal burden of CSVD-related cognitive impairment, targeted therapeutic research remains limited. Current interventions predominantly derive from VaD studies, where cholinesterase inhibitors (eg, donepezil, rivastigmine, and galantamine) are used to enhance synaptic acetylcholine levels and mitigate amyloid β protein generation and deposition, thereby ameliorating cognitive dysfunction [17-21]. While these agents demonstrate modest cognitive benefits, they are associated with clinically significant adverse effects, including severe gastrointestinal disturbances (eg, nausea and vomiting), dizziness, and bradycardia [22,23]. Other pharmacotherapies with putative efficacy in vascular cognitive impairment (VCI), such as *Ginkgo biloba* extracts and nimodipine, require further validation through randomized controlled trials (RCTs) [24,25]. Traditional Chinese medicine (TCM) offers a unique therapeutic paradigm for CSVD. The yin deficiency and blood stasis theory constitute the principal TCM pathogenesis framework, positing dual involvement of the kidney and brain. Guided by this theory, the zishenyizhi decoction (nourishing the kidney and enhancing intelligence decoction) has been empirically used to modulate CSVD progression.

Preliminary clinical studies have demonstrated that zishenyizhi decoction significantly improves cognitive dysfunction in patients with CSVD, as evidenced by enhanced scores on the Mini-Mental State Examination (MMSE), Instrumental Activities of Daily Living Scale, National Institutes of Health Stroke Scale, and TCM syndrome evaluation metrics. Preclinical investigations using rodent models of chronic cerebral hypoperfusion further revealed that this formulation ameliorates ischemia-hypoxia–induced pathological changes, enhances spatial learning and memory performance, and reduces hippocampal damage. This prescription has been transformed into the Chinese patent medicine zishenyizhi pill and is widely used in clinical practice due to its clinical efficacy. The zishenyizhi pill is composed of 11 herbs, with the composition and functions shown in Table 1. However, the precise molecular mechanisms underlying its neuroprotective and cognitive-enhancing properties in CSVD are yet to be fully elucidated.

Real-world studies originating from pragmatic clinical trials within the domain of pharmacoepidemiology involve large-scale, long-term evaluations of therapeutic interventions under routine clinical practice conditions. These studies prioritize clinically meaningful outcome measures to assess both efficacy and safety, with a primary emphasis on external validity [26]. In contrast, RCTs focus on internal validity by investigating highly selected populations under strictly controlled experimental settings [27,28]. RCTs are conducted under the premise that findings derived from selected study populations can be generalized to broader target populations. This study design is widely regarded as the gold standard for generating high-reliability evidence, with most clinical guidelines formulating recommendations based on outcomes extrapolated from RCT data [29]. However, a critical limitation stems from the stringent inclusion and exclusion criteria, which may result in study cohorts that inadequately reflect real-world clinical populations and compromise generalizability to broader patient groups. Such restricted participant selection introduces selection bias [30,31]. Due to the particularity and complexity of its theoretical system, through preliminary exploration, we believe that real-world studies are more suitable for the field of TCM. Therefore, we will conduct a real-world study on the treatment of cognitive impairment in CSVD (syndrome of yin deficiency and blood stasis) with zishenyizhi pill. The aim is to clarify the clinical efficacy and medication characteristics of zishenyizhi pill in treating patients with cognitive impairment due to CSVD and provide evidence-based support for its use.

**Table 1 table1:** Composition, effects, and pharmaceutical action of the Chinese herbal medicines that constitute zishenyizhi pill.

Chinese name	Latin name	Plant part	Effect (TCM^a^)	Pharmaceutical action	Dose (g)
Heshouwu	*Pleuropterus multiflorus*	Fruit	Nourishes essence and blood	Antioxidation, hypolipidemia regulation, and hepatoprotection	5
Gouqizi	*Lycii fructus*	Fruit	Nourishes the liver and kidney	Immunoregulation, anti-inflammation, and liver protection	5
Sangshen	*Mori fructus*	Fruit	Nourishes yin and blood and promotes fluid	Immunoregulation and antioxidation	5
Yinxingye	*Ginkgo biloba*	Leaf	Promotes blood circulation for removing blood stasis and obstruction in collaterals	Antioxidation, neuroprotection, and anti-inflammation	5
Danshen	*Salviae miltiorrhizae*	Root	Promotes blood circulation for removing blood stasis and obstruction in collaterals	Neuroprotection, antioxidation, and improvement of microcirculation	6
Yizhiren	*Alpinia oxyphylla*	Fruit	Nourishes the spleen and kidney	Neuroprotection, memory enhancement, and anti-inflammation	5
Shichangpu	*Acorus tatarinowi*	Tuber	Harmonizes the stomach, resolves phlegm, and opens the orifices	Neuroprotection, anticonvulsion, and antioxidation	5
Yujin	*Curcuma aromatica*	Tuber	Promotes qi circulation, activates blood flow, and alleviates pain	Anticancer, anti-inflammation, and antioxidation	5
Yuanzhi	*Polygala tenuifolia Willd.*	Root	Sedates the heart to stabilize the spirit and resolves phlegm to restore consciousness	Neuroprotection, antidepression, anti-inflammation, and antioxidation	5
Quanxie	Karsch *Olivierus martensii*	Dry body	Dispels pathogenic wind for resolving convulsion	Analgesia, anti-inflammation, and neuroprotection	1
Shanzha	*Crataegi fructus*	Fruits	Harmonizes the stomach and aids digestion	Neuroprotection	5

^a^TCM: traditional Chinese medicine.

## Methods

### Study Setting

This multicenter prospective observational nonrandomized controlled study (registered at the International Traditional Medicine Clinical Trial Registry; ITMCTR2025000553) enrolled 246 patients with CSVD-associated cognitive impairment of yin deficiency and blood stasis syndrome from 4 institutions—Hunan Provincial Hospital of Integrated Traditional Chinese and Western Medicine, Yiyang First Hospital of Traditional Chinese Medicine, Liuyang Hospital of Traditional Chinese Medicine, and Shimen County Hospital of Traditional Chinese Medicine. Eligible participants were stratified into 2 groups based on zishenyizhi pill use: the intervention group received guideline-based conventional Western medical therapy combined with zishenyizhi pill for 12 weeks, whereas the control group received guideline-based conventional integrated Chinese-Western therapy. Treatment for all enrolled participants was initiated during the stable phase of their outpatient visit or inpatient stay, immediately following the baseline assessment and confirmation of eligibility. Over the 12-week study period, multidomain cognitive assessments (executive function, attention, and processing speed) were conducted to evaluate the efficacy of zishenyizhi pill in CSVD-related cognitive impairment and explore its underlying mechanisms. The trial workflow is summarized in Figure 1. The evaluations and visits will be conducted according to the testing schedule in Table 2.

**Figure 1 figure1:**
[figure not shown]
Flowchart of the study.

**Table 2 table2:** Study timeline.

Assessment		Baseline	Midpoints		End point
		0 wk	4 wk	8 wk	12 wk
Informed consent		✓			
Inclusion criteria		✓			
Exclusion criteria		✓			
General information		✓			
Medical history		✓			
TCM^a^ syndrome criteria		✓			✓
**Primary outcome measure**					
	MoCA^b^	✓			✓
**Secondary outcome measures**					
	VaDAS-cog^c^	✓	✓	✓	✓
	MMSE^d^	✓	✓	✓	✓
	TMT-A^e^	✓	✓	✓	✓
	TMT-B^f^	✓	✓	✓	✓
	BNT-2^g^	✓	✓	✓	✓
	HVLT^h^	✓	✓	✓	✓
	CDT^i^	✓	✓	✓	✓
	IADL^j^	✓	✓	✓	✓
	EQ-5D-5L	✓	✓	✓	✓
	NPI^k^	✓	✓	✓	✓
	HADS^l^	✓	✓	✓	✓
	TCM syndrome criteria	✓	✓	✓	✓
**Safety assessments**					
	Blood, urine, and stool routine test	✓	✓	✓	✓
	Liver and kidney function	✓	✓	✓	✓
	Coagulation function	✓	✓	✓	✓
	Electrolytes	✓	✓	✓	✓
	Cardiac enzymes	✓	✓	✓	✓
	Lipid profile	✓	✓	✓	✓
	Blood glucose	✓	✓	✓	✓
	ECG^m^	✓	✓	✓	✓
	Efficacy evaluation		✓	✓	✓

^a^TCM: traditional Chinese medicine.

^b^MoCA: Montreal Cognitive Assessment.

^c^VaDAS-cog: Vascular Dementia Assessment Scale cognitive subscale.

^d^MMSE: Mini-Mental State Examination.

^e^TMT-A: Trail Making Test part A.

^f^TMT-B: Trail Making Test part B.

^g^BNT-2: Boston Naming Test–Second Edition.

^h^HVLT: Hopkins Verbal Learning Test.

^i^CDT: clock drawing test.

^j^IADL: Instrumental Activities of Daily Living Scale.

^k^NPI: Neuropsychiatric Inventory.

^l^HADS: Hospital Anxiety and Depression Scale.

^m^ECG: electrocardiogram.

### Training of Assessors and Quality Control

To ensure the consistency and reliability of the cognitive assessments, all neuropsychological evaluators across the 4 centers underwent centralized, standardized training before study initiation. Training sessions covered detailed administration protocols, scoring criteria, and interpretation guidelines for each cognitive tool (eg, Montreal Cognitive Assessment [MoCA], MMSE, Vascular Dementia Assessment Scale cognitive subscale [VaDAS-cog], and Trail Making Test parts A [TMT-A] and B [TMT-B]). Calibration exercises were conducted to minimize interrater variability, and periodic quality checks were implemented throughout the study.

### Participants

This study focuses on patients with cognitive impairment due to CSVD with TCM syndrome of yin deficiency and blood stasis treated in the outpatient and inpatient departments of 4 institutions: Hunan Provincial Hospital of Integrated Traditional Chinese and Western Medicine (affiliated hospital of Hunan Academy of Chinese Medicine), Yiyang First Hospital of Traditional Chinese Medicine, Liuyang Hospital of Traditional Chinese Medicine, and Shimen County Hospital of Traditional Chinese Medicine.

### Inclusion Criteria

The inclusion criteria are as follows: (1) Western medicine diagnosis meeting the diagnostic criteria for CSVD-associated cognitive impairment, (2) TCM syndrome meeting the yin deficiency and blood stasis syndrome criteria (the Dementia Syndrome Differentiation and Classification Scale is used for syndrome judgment, and the syndrome is established when the score is ≥7; the rating details are shown in Multimedia Appendix 1), (3) age ≥60 years, and (4) agreement from the patients or their family members and signature of an informed consent form.

### Exclusion Criteria

The exclusion criteria are as follows: (1) coexisting neurological disorders causing cognitive impairment, including Alzheimer disease, frontotemporal dementia, Lewy body dementia, Parkinson disease, multiple sclerosis, traumatic brain injury, autoimmune disorders, or genetic diseases; (2) impaired consciousness, unstable vital signs (eg, blood pressure, respiratory rate, or heart rate), or life-threatening conditions (such as severe cardiac, hepatic, renal, or endocrine disorders); (3) inability to comprehend or comply with study procedures or follow-up due to psychiatric illnesses, cognitive or emotional disorders, or severe visual or auditory impairments; (4) severe hepatic or renal dysfunction (alanine transaminase or aspartate transaminase of >2 times the upper normal limit; creatinine of >1.5 times the upper normal limit); (5) previous use of kidney-nourishing or blood-activating herbal therapies within 2 weeks before enrollment; and (6) hypersensitivity to any component of the zishenyizhi pill.

### Recruitment of Participants

All participants will be recruited through posters from inpatients and outpatients of 4 institutions: Hunan Provincial Hospital of Integrated Traditional Chinese and Western Medicine (affiliated hospital of Hunan Academy of Chinese Medicine), Yiyang First Hospital of Traditional Chinese Medicine, Liuyang Hospital of Traditional Chinese Medicine, and Shimen County Hospital of Traditional Chinese Medicine.

### Interventions

All participants were stratified into 2 groups based on zishenyizhi pill administration: the intervention group and the control group, each comprising 123 patients. Both groups received standardized Western pharmacological therapy, including antihypertensive treatment, antiplatelet therapy, and lipid-lowering therapy. The intervention group additionally received the zishenyizhi pill at a dosage of twice daily for 12 consecutive weeks.

### Outcomes

#### Primary Outcome

The MoCA assessed the degree of global cognitive function at baseline and 12 weeks after the intervention.

#### Secondary Outcomes

The VaDAS-cog assessed the degree of attention, executive function, and related cognitive domains at baseline and 12 weeks after the intervention. The MMSE assessed the degree of orientation, memory, and calculation ability at baseline and 12 weeks after the intervention. The TMT-A assessed the degree of visuospatial ability, psychomotor speed, and visual attention at baseline and 12 weeks after the intervention. The TMT-B assessed the degree of executive function, processing speed, and cognitive flexibility at baseline and 12 weeks after the intervention. The Boston Naming Test–Second Edition assessed the degree of language function (naming ability) at baseline and 12 weeks after the intervention. The Hopkins Verbal Learning Test assessed the degree of memory function (verbal memory) at baseline and 12 weeks after the intervention. The clock drawing test assessed the degree of visuospatial skills and executive function at baseline and 12 weeks after the intervention. The Instrumental Activities of Daily Living Scale assessed the degree of functional independence in daily living at baseline and 12 weeks after the intervention. The EQ-5D-5L assessed health-related quality of life at baseline and 12 weeks after the intervention. The Neuropsychiatric Inventory assessed the severity of neuropsychiatric symptoms at baseline and 12 weeks after the intervention. The Hospital Anxiety and Depression Scale assessed the severity of anxiety and depressive symptoms at baseline and 12 weeks after the intervention. The TCM syndrome criteria assessed the severity of TCM syndromes at baseline and 12 weeks after the intervention.

### Safety Evaluation and Adverse Events

Safety assessments included electrocardiogram, blood routine tests, liver function tests, renal function tests, cardiac enzyme level, blood glucose level, lipid profile, urine test, and stool routine test. Adverse events were comprehensively documented in case report forms (CRFs) throughout the study period. Serious adverse events—defined as those resulting in disability, operational incapacity, life-threatening conditions, or death—required immediate notification to both the investigators and the ethics committee. The research team provided clinical guidance and therapeutic interventions to affected participants while determining their eligibility for continued study participation.

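### The serious-adverse-event definition leaves out hospitalisation and other medically important events, so some of these carry no serious label and no required prompt notification in either group

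*Protocol article*

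**What the plan says.** The rule is in the protocol article, Methods, Safety Evaluation and Adverse Events: "Serious adverse events—defined as those resulting in disability, operational incapacity, life-threatening conditions, or death—required immediate notification". The notice goes to two parties, as the same sentence continues: "immediate notification to both the investigators and the ethics committee". For adverse events in general the section says: "Adverse events were comprehensively documented in case report forms (CRFs) throughout the study period". Its last sentence has the research team advise and treat affected participants and decide whether they may stay in the study. It is unclear whether that covers every adverse event or only serious ones.

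Other parts of the article bear on the point:

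- Abstract, Objective: "We designed this study to evaluate the real-world efficacy and safety of zishenyizhi pill combined with conventional Western therapy". The Abstract's Conclusions already anticipate that the pill will help "while demonstrating a favorable safety profile".
- Study Setting: "Treatment for all enrolled participants was initiated during the stable phase of their outpatient visit or inpatient stay".
- Inclusion Criteria: participants are aged 60 or over.
- Interventions: "Both groups received standardized Western pharmacological therapy, including antihypertensive treatment, antiplatelet therapy, and lipid-lowering therapy".
- Table 2, safety assessments: "Liver and kidney function", coagulation, routine blood tests and others are scheduled at weeks 0, 4, 8 and 12.

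**The concern.** The sentence is worded as a definition. It has no opening such as *for example* and no closing category for other important events. Both the serious label and the duty to notify promptly hang on it.

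The population makes the omission matter. Participants are older, all are meant to receive antiplatelet treatment among other drugs, and some start treatment while in hospital. A new admission or a delayed discharge is a realistic consequence of an adverse event here. Such an event can be clinically weighty without killing, threatening life or leaving lasting disability.

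Two things are at stake. One is participant protection: the ethics committee may not hear promptly of events that it would want to know about. The other is the reading of the safety objective: any later statement about how many serious events occurred would rest on a narrow definition, and a low count would be hard to interpret.

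**Working it through.** No formula applies. The check is one of wording, in four steps.

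**1. What the list contains.** There are four criteria: disability, operational incapacity, threat to life, and death. The sentence has no open-ended wording.

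**2. Whether another section widens it.** The remaining sections, including Table 2, Outcomes, Combination Medications, Statistical Analysis and Data Management and Quality Control, contain no further seriousness criterion and no other prompt-notification route. The rule makes no distinction between the groups.

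**3. Applying the rule to plausible events.** The cases below are hypothetical. Each is assumed not to threaten life, disable or kill.

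| Event | Recorded on CRF | Serious by the listed criteria | Immediate notification required |
|---|---|---|---|
| Bleed on antiplatelet therapy, admitted, recovers | Yes | Only if *operational incapacity* is read to cover it | Same condition |
| Liver injury leading to admission | Yes | Same condition | Same condition |
| Inpatient at entry whose discharge is delayed by an adverse event | Yes | Same condition; no rule on prolongation | Same condition |
| Medically important event managed without admission | Yes | Same condition | Same condition |

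In every row the answer turns on one undefined term. Read narrowly, none of the four is serious; read broadly, some are. Four centres can apply it differently.

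**4. Whether the scheduled tests close the gap.** They can reveal a liver, kidney, clotting or blood-count abnormality. They are 4 weeks apart, however, and a test result neither assigns the serious label nor sets off a notification.

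**Size.** The count of affected events would need the rate of admissions, prolonged stays and medically important events, and the share that falls outside the four criteria. The article gives neither, so no figure can be derived.

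**The case against.** The strongest reply has four parts.

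- **The yardstick is not in the document.** The article cites no standard that requires hospitalisation as a criterion, and no section contradicts the definition. This stands in part. The point is a judgement that the list is too narrow for this population and this objective; it is not a demonstrated internal error.
- **The article condenses a fuller protocol.** Seriousness criteria and reporting forms often sit there, and sites may already work from something wider. That is possible. But the article is not silent: it states a specific definition and ties a duty to it. If the full protocol differs, the published wording still needs correcting.
- **The undefined term may already cover many admissions.** It may cover some. That argues for defining it rather than relying on it.
- **Nothing is lost.** All adverse events are documented, the team cares for affected participants, laboratory and electrocardiogram checks recur, and neither Outcomes nor Statistical Analysis sets out a comparison of serious events. All of this is correct and limits the consequence. It leaves untouched the missing label and the missing duty of prompt notice.

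A reader might infer more than this, and the article does not support it. It does not say that these events go unrecorded, nor that sites may not report them promptly; it only fails to require it. It does not show that the gap favours the pill, since one rule covers both groups. Nor does it show that a planned between-group comparison of serious events would be distorted, because it describes none.

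**Conclusion.** The point holds in this limited form. As written, adverse events that require or prolong hospitalisation, or are otherwise medically important, and that meet none of the four criteria are recorded without a serious label and without any required immediate notification, in both groups. Their number cannot be derived, and it depends on how *operational incapacity* is read.

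The conclusion rests on two assumptions: that the published definition is the one the sites follow, and that events of this kind should reach the investigators and ethics committee promptly in a study of older inpatients and outpatients. The MoCA analysis is unaffected. It is a cheap improvement to participant oversight and to the reading of the safety objective.

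**What to change.** Amend the definition in Safety Evaluation and Adverse Events as follows:

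- Add two criteria: *requires or prolongs unplanned hospitalisation* and *other medically important event*.
- State that the inpatient stay during which a participant enters the study does not count, and that pre-planned or elective admissions do not count, but that prolongation of the entry stay does.
- Define *operational incapacity* in one phrase.

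Apply the amended definition prospectively in both groups. The Results section reports 47 participants enrolled by November 2025, 28 of whom had completed follow-up, so 246 − 47 = 199 were still to be enrolled at that date. These figures describe the reach of an amendment, not the size of the defect. For participants already enrolled, re-classify recorded adverse events by the same criteria in both groups, as far as the CRFs or existing hospital records show an admission or a prolonged stay.

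The costs are somewhat more reports to the ethics committee and possibly a higher serious-event rate. The CRF is not shown, so it cannot be assumed to record admission. If it does not, one field must be added, or source records checked at the four hospitals. No study visit, laboratory test or efficacy analysis changes.
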